### Feasibility of the study design

A pilot study was conduced between June 2006 and December 2006 to evaluate the feasibility of the measurements, randomisation-procedure and treatment protocols (33). The recruitment of participants for this pilot-study took place in two primary health-care centers in The Netherlands. A total of 20 patients were randomised to either the GP or the MT intervention group. Thirty-one patients who had a strong preference for the manual therapy intervention and could not be randomised were asked to participate in a parallel cohort-study. In this study similar baseline and follow up measurements were conducted.

The results of the pilot study showed that the procedures were feasible. The research-assistants, general practitioners and manual therapists reported having no problems to adhere to the guidelines and protocols for measurements and treatment. In order to include a total of 80 patients over a period of one year, 32 GPs and 4 MTs have been recruited to participate in the full trial.

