### Sample size

In a pilot study the 2 weeks headache diary showed an average of 11 days with headache in both treatment groups at baseline. After 8 weeks the frequency of days with headache in the GP group was reduced to 7 days, in the MT group to 3 days. In the full trial we aim to detect a difference in reduction of at least 3 days (SD 5) between both groups. To detect this difference with a one-sided significance level of 0.05, and power of 0.80 we have to include at least 35 patients in each treatment group. The participants in the pilot study reported taking on average 2 doses of NSAID or analgesics per 2 weeks. With a sample size of 35 patients per group we can detect a difference of at least 0.5 (SD 0.8) doses per 2 weeks between the groups. With a calculated loss of participants in the full trial of 15%, this trial attempts to enroll forty-two patients with CTTH in each treatment groups (GP, MT).

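### The sample size section calls for 84 patients but recruitment was organised for 80, which after the planned 15% loss leaves 34 per arm against a stated minimum of 35 (minor)

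*Protocol article*

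**What the plan says.** The Sample size section of the protocol article builds the enrolment figure in three steps.

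- Assumptions for headache days: "we aim to detect a difference in reduction of at least 3 days (SD 5) between both groups", tested "with a one-sided significance level of 0.05, and power of 0.80".
- Minimum: "we have to include at least 35 patients in each treatment group".
- Allowance for loss: 15%, from which the enrolment aim is derived: "this trial attempts to enroll forty-two patients with CTTH in each treatment groups (GP, MT"). Two groups of 42 make 84.

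For medication use, the same section says of 35 per group that "we can detect a difference of at least 0.5 (SD 0.8) doses per 2 weeks between the groups".

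The section on feasibility of the study design first reports the pilot study and then turns to the full trial. It gives the recruitment goal as follows: "In order to include a total of 80 patients over a period of one year". The capacity arranged for that goal is 32 GPs and 4 manual therapists.

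**The concern.** The article gives two enrolment totals for the same trial, 84 and 80, and explains neither by the other. The 80 cannot be a pilot or cohort figure: the pilot randomised 20 patients, 31 more entered a parallel cohort, and the sentence with 80 refers to the full trial. Nor is it the number to be analysed, since 2 × 35 = 70.

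The lower total matters because it does not deliver the article's own minimum once the article's own loss rate is applied. The Discussion names inclusion as the hardest part of the study, so the target should be unambiguous. A later reader who wants to know whether enrolment was completed as planned has two answers to choose from.

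**Working it through.** **Inputs.** From the Sample size section: difference 3 days, SD 5 (taken as the common within-group SD of the change), one-sided α = 0.05, power 0.80, minimum 35 per group, loss 15%, enrolment 42 per group; for medication, difference 0.5 doses, SD 0.8. From the feasibility section: total 80, 32 GPs, 4 manual therapists.

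**1. Reproduce the minimum.** Normal approximation:

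n per arm = 2 × (z₀.₉₅ + z₀.₈₀)² × (SD/difference)² = 2 × (1.645 + 0.842)² × (5/3)² ≈ 34.4, rounded up to 35.

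The t-test solution is 35.04. The stated 35 is reproduced.

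**2. Reproduce the enrolment figure.** 35 / (1 − 0.15) = 41.2, rounded up to 42 per arm; 2 × 42 = 84. The stated 42 is reproduced.

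**3. Look for a route to 80.** The cruder inflation, 35 × 1.15 = 40.25, rounds up to 41 per arm, 82 in total. Only rounding it down gives 40 per arm and 80. The article does not describe that step, and it conflicts with the 42 that the article does state.

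**4. Expected number retained, equal arms and equal loss.**

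| Enrolled | Per arm | × 0.85 | Against the minimum of 35 |
|---|---|---|---|
| 80 | 40 | 34.0 | 1 short |
| 84 | 42 | 35.7 | met |

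The largest loss that still leaves 35 per arm is 1 − 35/40 = 12.5% with 80 enrolled and 1 − 35/42 = 16.7% with 84. The planned 15% lies between the two.

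**5. One-sided power for headache days (3/5 = 0.6).** The normal approximation is Φ(0.6 × √(n/2) − 1.645). At n = 34: 0.6 × √17 = 2.474, and Φ(0.829) = 79.6%.

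| Per arm | Normal approximation | t-test |
|---|---|---|
| 34 | 79.6% | 78.9% |
| 35 | 80.7% | 80.0% |
| 35.7 | 81.3% | 80.7% |

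**6. One-sided power for medication use at 34 per arm (0.5/0.8 = 0.625).** Φ(0.625 × √17 − 1.645) = Φ(0.932) = 82.4%; by t-test 81.7%.

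**The case against.** The strongest reply is that only the Sample size section states an enrolment aim. The 80 stands in a clause that explains how many practitioners were recruited, and it may be a round planning figure for one year. Staffing would hardly differ: 80/32 = 2.5 patients per GP against 84/32 = 2.6, and the article gives no recruitment rate by which 32 GPs would suffice for 80 but not for 84. The expected shortfall is one patient per arm, disappears if loss is 12.5% or less, and costs about one percentage point of power.

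Most of this stands, and it limits the point to a minor one. It does not remove the contradiction: the text does not mark 80 as approximate, and taken at face value with the planned loss it misses the stated minimum.

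Two stronger readings do not hold.

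- A reader might infer that recruitment will close at 80, or after one year. The article contains no such rule.
- A reader might add that two-sided power at 34 per arm is only 68.4% and count that against the lower total. The calculation is specified as one-sided, and two-sided power is already 69.7% at 35 per arm and 70.5% at 35.7. Nearly all of the gap from 80% comes from the sidedness of the test, so it is not a consequence of 80 versus 84.

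**Conclusion.** The article states two enrolment totals that differ by 4 patients (4/84 = 4.8%), and the lower one leaves 34 per arm where at least 35 are required. This rests on equal allocation, which follows from 42 in each group, and on the planned 15% loss falling equally on both arms.

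The size is small. One-sided t-test power for headache days would be about 78.9%, which is 1.1 points below that at 35 per arm and 1.8 points below that at 35.7 (80.7 − 78.9). The medication outcome stays above 80%. The sample size calculation reproduces and is not in question; neither the design nor the analysis is affected. This is a minor inconsistency that should be corrected.

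**What to change.** In the feasibility section, replace 80 with 84 (42 per arm), so that the article states one enrolment target and agrees with its Sample size section. This changes one figure and needs no new calculation.

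If 80 is the intended target, change the Sample size section instead: 40 per arm enrolled, 34 per arm expected evaluable after 15% loss, and one-sided power of about 79% for 3 days (SD 5). That costs a few words and an open statement that the expected number falls one short of 35 per arm.

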## Discussion

We have described the design of a RCT to evaluate the effectiveness manual therapy compared to GP usual care for patients with CTTH. Both approaches are commonly used: most GPs will consult recommendations by the national clinical guideline when managing patients with headache. The manual therapy intervention is based on a treatment protocol developed in consensus with the participating MTs, and consists of commonly used mobilisation techniques and exercises. This pragmatic design will increase the external validity of the results of this trial. The MT treatment is assumed to improve cervical and thoracic spine movement and function, leading to a decrease in the frequency of headache-days. The education and exercise-training in this program is focused on self-mangement and postural correction, and aims for a sustained long-term effect. Although van Ettekoven et al [34] reported beneficial effects of a craniocervical training program for patients with CTTH, it still remains unclear what mechanisms may explain these effects. Measurement of the neckflexor muscle endurance, active range of motion of the cervical spine and the craniocervical angle in our study will provide more information on assumed processes during treatment.

This trial has a few limitations. The first limitation is the limited possibilities for blinding. Double blinding procedures in a pragmatic study cannot be obtained, and it is not possible to blind the participating GPs, MTs and patients for intervention. We do hope to reduce the risk of information bias by using standardised procedures and assessment by a blinded research assistant. The second limitation of this pragmatic trial concerns the difference in time spent on the patients' treatment by the GP and MT. It is unclear to what extent this time-factor will attribute to the overall effect of manual therapy.

Inclusion of a sufficient number of eligible patients for the RCT will be the most difficult element of this study. Rasmussen et al described a low consultation rate in patients with CTTH: only twenty percent will consult their GP [4]. The GPs will have to identify these patients during office hours and inform them about the trial. This method of recruitment has been reported to be associated with low recruitment rates.[35] In order to optimize the inclusion of patients the GPs and healthcare centers receive 'newsletters' and visits from the researcher on a regular basis to obtain the full participation in the trial.

The pilot study demonstrated a preference for manual therapy in the majority of patients. For patients who do not consent to randomisation we will conduct a parellel cohort-study alongside the trial to monitor outcome this group of patients. Expectations regarding the result of treatment will be asked for all participants in both trial and cohort, in order to estimate the potential influence of these expectations on outcome.

To publish an article of a study design has some advantages. Publication bias can be prevented whereby only studies producing positive results are more likely to be published.[36] It also offers an opportunity to reflect critically on the study design, independently of the results.

In this trial we will evaluate and compare two treatment protocols (GP, MT) that reflect 'usual care' for patients with CTTH. Therefore, the results of this pragmatic trial will contribute to clinical decision making by the GP in patients with CTTH, providing information on the potential benefits of a referral for manual therapy in primary care in the Netherlands.
